#### Drop-out visit:

- Ataxia rating scales (SARA, SCAFI)
- Self-administered questionnaires (EQ-5D-5L, BDI-II, FSS)
- Documentation of adverse events
- Documentation of frequency of physiotherapy and speech therapy (hours per week)
- Documentation of concomitant medication
- Blood test including pregnancy test for women of child bearing potential

## **11 Safety Data Collection, Recording and Reporting**

### **11.1 Definitions**

#### **Adverse Event (AE)**

An Adverse Event/Experience (AE) is any untoward medical occurrence in a patient or in a clinical investigation subject administered a pharmaceutical product and which does not necessarily have a causal relationship with this treatment.

An AE can therefore be any unfavorable and unintended sign (including an abnormal laboratory finding), symptom or disease temporally associated with the use of a medicinal product, whether or not related to the treatment.

#### **Adverse (Drug) Reaction (AR)**

In the pre-approval clinical experience with a new medicinal product or its new usages, particularly as the therapeutic dose(s) may not be established, all noxious and unintended responses to a medicinal product related to any dose should be considered adverse drug reactions. The phrase responses to a medicinal product means that a causal relationship between a medicinal product and an adverse event is at least a reasonable possibility, i.e. the relationship cannot be ruled out.

Regarding marketed medicinal products: a response to a drug which is noxious and unintended and which occurs at doses normally used in man for prophylaxis, diagnosis, or therapy of diseases or for modification of physiological function

#### **Unexpected Adverse (Drug) Reaction (UAR)**

An adverse reaction, the nature or severity of which is not consistent with the applicable product information (e.g., Investigator's Brochure for an unapproved investigational product or package insert/Summary of Product Characteristics for an approved product)

**Serious Adverse Event (SAE)**

Any untoward medical occurrence that at any dose:

- results in death
- is life-threatening
- requires inpatient hospitalization or prolongation of existing hospitalization
- results in persistent or significant disability/incapacity or
- is a congenital anomaly/birth defect
- is qualified as another medically significant event or condition

**Serious Adverse (Drug) Reaction (SAR)**

This is defined as an adverse drug reaction that is serious (see SAE criteria above) and at least possibly related to the IMP.

**Suspected Unexpected Serious Adverse (Drug) Reaction (SUSAR)**

A SUSAR is an adverse reaction, which is suspected, serious and unexpected because the nature or severity of this event is not consistent with the applicable product information (e.g. Summary of Product Characteristics for an authorized product or Investigator's Brochures for an unauthorized investigational medicinal product).

See also section Assessment of Seriousness (11.2.2).

**11.2 Criteria to be evaluated by the investigator (1st assessment)**

Special attention is to be paid to the occurrence of adverse events (AE) throughout every stage of the clinical trial. The investigator should evaluate all adverse events according to the criteria and steps mentioned below.

**11.2.1 Assessment of Intensity**

|                                                             |                                                                                                                            |
|-------------------------------------------------------------|----------------------------------------------------------------------------------------------------------------------------|
| Any adverse event has to be graded regarding its intensity. |                                                                                                                            |
| MILD                                                 | Does not interfere with subject's usual function, easily tolerated.                                                        |
| MODERATE                                             | Interferes to some extent with subject's usual function.                                                                   |
| SEVERE                                               | Interferes significantly with subject's usual function, incapacitating with inability to work or carry out usual activity. |

**Confidential**

### 11.2.2 Assessment of Seriousness

Determination of the seriousness of the adverse event according to the definitions for a serious adverse event (SAE) as given in section Definitions (see 11.1).

### 11.2.3 Assessment of Causality

Determination of the relationship of the adverse events to the medicinal product(s) being studied after having evaluated all accessible data according to the following classification:

#### **Suspected:**

The temporal relationship between the event and the administration of the IMP makes a **causal relationship possible, probable, or definite**, or other drugs, therapeutic interventions or underlying conditions do not provide a sufficient explanation for the observed event.

#### **Not suspected:**

The temporal relationship between the event and the administration of the IMP makes a **causal relationship unlikely or impossible (i.e. not related)**, or other drugs, therapeutic interventions or underlying conditions provide a sufficient explanation for the observed event.

When the final causality assessment is unknown and it is **uncertain** whether or not the investigational product caused the event, then the event should be handled as an SAE **related** (suspected) to the investigational product for reporting purposes.

### 11.3 Criteria to be evaluated by the Sponsor Delegated Person (2nd assessment)

In addition to the first evaluation of an adverse event that is performed by the investigator, a second evaluation with respect to seriousness, causality and expectedness and a risk-benefit assessment is performed by the Sponsor Delegated Person or an authorized representative to process safety evaluation according to a four-eyes principle.

### 11.4 Documentation and Reporting of Adverse Events

Any AE has to be documented in the CRF on the respective Adverse Event Report Form.

Documentation and evaluation of each AE occurring between:

- starting with first study specific intervention up to 30 days after the subject has received the last dose of trial drug

**Confidential**

## 11.5 Documentation and Reporting of Serious Adverse Events

Any SAE has to be reported immediately to Winicker Norimed.

Documentation and evaluation of each SAE occurring:

- starting with first study specific intervention up to 30 days after the subject has received the last dose of trial drug.

### 11.5.1 Initial Reporting of SAEs

Any SAE has to be documented on the respective Serious Adverse Event Report Form, provided by Winicker Norimed to all investigators. The investigator has to

Report the SAE to WINICKER NORIMED GmbH

[name]

[name]

Deutschland

**IMMEDIATELY**

after becoming aware of this event

**(latest within 24 hours)**

**[contact] – [name]**

### 11.5.2 Reporting to the authorities and ethics committees

The SAEs of a clinical trial have to be notified to the competent authority once a year or on request.

Depending on the sort of the SUSAR the SDP has to consider special timelines for reporting to the competent authorities and ethics committees. The following timelines have to be considered for reporting of SUSARs to CA and EC:

**Confidential**

**Fatal or life-threatening SUSARs:**

- as soon as possible, at the latest within 7 calendar days after first knowledge of the minimum criteria

**Non-fatal and non-life-threatening SUSARs:**

- as soon as possible, at the latest within 15 calendar days after first knowledge of the minimum criteria.

In multicenter trials the principal investigators of all other investigator sites will be informed about each SUSAR. All these tasks are delegated to Winicker Norimed by the SDP.

## **11.6 Pregnancy**

Women of childbearing potential are required to have a negative pregnancy test to exclude a pregnancy before being randomized in the clinical trial.

Pregnancy testing will be conducted at the time points specified in the schedule of activities (see 2).

### **11.6.1 Actions to be taken if pregnancy occurs to female subjects or partners of male subjects**

If a female subject becomes pregnant or is suspected to be pregnant (including a positive pregnancy test regardless of age or disease state) while participating in this trial and taking the study drug, or within 30 days of the last dose of the study drug, the investigator has to be informed immediately about this event. The pregnant subject has to discontinue the treatment with the IMP permanently, has to be excluded from the trial and has to be instructed to return any unused portion of the study drug to the investigator, if applicable. Likewise, if the partner of a male trial subject becomes pregnant or is suspected to be pregnant while the subject participates in this trial, the investigator has to be informed immediately about this suspected or confirmed pregnancy. The investigator will then provide this information to the sponsor /sponsor-delegated person for follow-up as necessary.

To ensure the safety of female subjects or female partners of male subjects, each pregnancy that becomes known to the investigator during the trial must be reported as an event. Therefore the investigator will record and report pregnancy information on the appropriate report form as an initial report and fax it immediately (at the latest within 24h) to WINICKER NORIMED GmbH

**[contact] – [name])**

The pregnancy itself is not considered to be an AE or SAE but must be followed up until delivery or until pregnancy termination and the outcome of pregnancy should be notified to the sponsor-delegated person to determine the outcome of the pregnancy regarding maternal or newborn complications. The investigator will seek and provide this follow-up information after the planned date of delivery. This information will be

**Confidential**

forwarded to the sponsor-delegated person. For this purpose the pregnancy report form will be used as follow-up report. The timeframe for following-up the details of birth will be no longer than 28 days after the delivery date.

If the outcome of the pregnancy includes

- a spontaneous, therapeutic abortion or voluntary termination
- stillbirth
- neonatal death
- presence of birth defects or
- congenital anomaly (including that in an aborted fetus, stillbirth or neonatal death)

the investigator should report this outcome as an SAE.

All neonatal deaths that occur within 28 days of birth should be reported as SAEs without regard to causality. In addition, any infant death after 28 days that the investigator suspects is related to the in utero exposure to the study drug should be reported. Furthermore, any SAE occurring as a result of a post-trial pregnancy and considered reasonably related to the investigational medicinal product by the investigator will be reported as described in this section. The investigator is not obliged to actively seek this information in former trial participants, but has to meet the reporting obligations as soon as the investigator is aware of this event through spontaneous reporting by the person concerned.

## 12 Data Safety Monitoring Board (DSMB)

A Data Safety Monitoring Board (DSMB) will be established to review accumulating safety data during the course of the trial. The DSMB may recommend discontinuation of the trial or modification of the protocol for safety reasons at any time during the trial. The decision to terminate is taken by the sponsor delegated person together with the coordinating investigator. The members will be chosen from different fields. The members will not be involved in the design of the study, its conduct other than through their role on the DSMB and will have no financial interest in the outcome of the study. The DSMB will have written operating procedures.

## 13 Statistical Methods

### 13.1 Planned Statistical Analyses

#### **Analysis of primary endpoint:**

For the primary outcome change in SARA total score (DeltaSARA), the null hypothesis will be tested that the mean change is the same on placebo and on acetyl-DL-leucine. The significance level alpha is set to 5%.

The primary efficacy analysis will be performed according to the intention-to-treat (ITT) principle. Absolute change calculated as the difference between the period-level baseline score and the score measured at the 2-week visit and at the 6-week visit of the verum/ placebo period will be considered for a model-based primary efficacy analysis. If not revised in the *statistical analysis plan* (SAP), a linear mixed effects model for DeltaSARA will be performed (fixed effects: factors for treatment and visit, treatment-by-visit interaction, mean of both period-level baseline SARA total scores as covariate; normally distributed patient-specific random intercepts) in order to deal with repeated measurements within periods and measurements not made at equivalent times on each subject (due to unscheduled or missed clinic visits). This subject-specific modelling approach allows individual change scores over time to be calculated. To analyse the differences between both treatments at the end of the 6-week treatment period, 95% confidence intervals will be provided to quantitatively describe treatment effects.

Sensitivity analyses will be performed on a per protocol approach which accounts for compliance with medication according to the protocol. Additional efficacy analyses adjusting for genetically vs. sporadic CA, gender, age, or trial site, will be performed. Besides, the robustness of the overall result will be investigated by sensitivity analyses adjusting for speech-/physiotherapy (as considered appropriate during the blinded data review depending on the data quality). Further methodological details will be provided in the SAP.

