## 7 Trial Design

### 7.1 Trial Design

The study is designed as a multinational, multicenter, prospective, randomized, double-blind, placebo-controlled, 2- period 2-treatment crossover phase III superiority trial with a fixed sample design.

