#### **Analysis of key secondary endpoints:**

In case of a statistically significant primary efficacy result, confirmatory testing will be extended to the EQ-5D-5L (VAS and descriptive scale). Two-sided tests for detecting treatment differences will be carried out.

SCAFI (total score and 3 subscores), SARA subscale items, as well as patient-reported outcomes BDI-II and FSS are not considered in the hierarchical multiple testing procedures. Descriptive comparisons between treatment groups at the end of the 6-week verum/ placebo period will be performed by use of a two-sided Wilcoxon signed rank test, and additionally, Hodges-Lehmann estimation of the location shift between the two groups will be provided, as considered appropriate based on the blinded data. The same non-parametrical tests will be employed to estimate treatment differences at the follow-up visit 8 (close-out visit).

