### 13.3 Sample Size Calculation

The sample size was calculated on the basis of the primary hypothesis, using own preliminary case series data (n=13 patients; [10]) and a similar placebo-controlled trial (N=20 patients; [31]) evaluating the efficacy of varenicline on the improvement in SARA total score in patients with SCA3.

Hence, assuming a minimum clinically relevant improvement in the SARA total score of 1.5 points [28] (the absolute change under verum is by 1.5 score points better as the change under placebo) and a standard deviation of the individual SARA change of 3.0 (which results in a standard deviation of 4.2 assuming an intra-patient correlation of 0.6), a **sample size of 86** (85 is calculated but 2 sequences are needed) **in total** is needed to have 90% power to detect a difference in means of 1.5, using a paired t-test with a 0.05 two-sided significance level [Software used: nQuery Advisor 7.0].

Assuming a dropout rate of about 20%, **a total of 108 patients have to be allocated to the trial**. With a proportion of about 50-55% recruited patients out of the number to be screened, 200 patients have to be assessed for eligibility.

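### The default primary model of this two-period crossover has no period term: a modest loss of precision, and a small bias if dropout differs by sequence

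*Protocol*

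**What the plan says.** Section 7.1 describes a "2- period 2-treatment crossover phase III superiority trial with a fixed sample design". The endpoint in section 6.2 is the change in SARA total score from each period's own baseline.

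Section 13.1 (analysis of primary endpoint) specifies a linear mixed model with normally distributed patient random intercepts and "fixed effects: factors for treatment and visit, treatment-by-visit interaction, mean of both period-level baseline SARA total scores as covariate". The Statistical Rationale in the synopsis gives the same terms. Neither place names period or sequence. The additional adjusted analyses listed in section 13.1 cover ataxia type, gender, age, trial site and speech or physiotherapy, but not period. The model stands unless the SAP changes it. The responses analysed are those at the 2-week and the 6-week visit of the verum or placebo period.

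For SCAFI, the SARA items, BDI-II and FSS, section 13.1 says that descriptive comparisons "will be performed by use of a two-sided Wilcoxon signed rank test", again without reference to period. Section 13.6 has the primary analysis use all observed data without imputation.

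**The concern.** In a two-period crossover each patient's verum-minus-placebo difference contains the treatment effect and any difference in mean change between the periods. The period part enters with opposite sign in the two sequences. A period term removes it. Nothing in the stated model can take its place: the random intercept and the mean of both baselines are constant within a patient, and a two-level visit factor takes the same two values in each period.

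The documents give some reason to allow for such a difference. SARA is rated at every visit, so practice or expectation may act differently early and late. A SARA score of at least 3 is an entry criterion and, when visits 1 and 2 coincide, one rating both selects the patient and serves as the period 1 baseline. That permits some regression to the mean in period 1 only, probably slight at so low a threshold.

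At stake are precision when the sequences stay balanced, and some bias in the treatment estimate when they do not.

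**Working it through.** **Inputs.** From section 13.3:
- two-sided 5% level: "using a paired t-test with a 0.05 two-sided significance level"
- target: "is needed to have 90% power to detect a difference in means of 1.5"
- SD of the within-patient difference 4.2; 86 completers; 108 randomised

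Section 8.5 gives 1:1 allocation, so 54 per sequence. Expected dropouts are 108 − 86 = 22. The period difference pi, meaning the mean change in period 2 minus that in period 1, is not in the protocol. A range of 0.5 to 2 points is assumed.

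**The plan's own figure.** A paired t-test with difference 1.5 and SD 4.2 needs n = 85 by the noncentral t distribution, in agreement with "85 is calculated but 2 sequences are needed". Power at 86 is 90.6%. Inflation for dropout: 86/0.80 = 107.5, so 108. The SD of 4.2 is used here because it reproduces the plan. It does not follow from the stated SD of 3.0 and correlation of 0.6, which give √(2 × 3.0² × 0.4) = 2.68; that is a separate matter.

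**Balanced sequences (43:43).** The differences have mean delta − pi in verum-first and delta + pi in placebo-first patients. The average is still delta, so there is no bias. Pooled over sequences, the variance becomes 4.2² + pi²:

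| pi | variance | SD | increase | power at n = 86 |
|---|---|---|---|---|
| 0 | 17.64 | 4.20 | – | 90.6% |
| 0.5 | 17.89 | 4.23 | 1.4% | 90.2% |
| 1 | 18.64 | 4.32 | 5.7% | 89.0% |
| 2 | 21.64 | 4.65 | 23% | 84.0% |

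These powers slightly overstate the loss, because pi enlarges the estimated SD but not the true sampling error of the mean. At pi = 1.5 the formula gives 86.9% (SD √19.89 = 4.46), whereas simulation gives 88.2%. For the same reason the test is conservative: simulated two-sided type I error at pi = 1.5 is 0.038.

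**Unbalanced sequences.** Suppose the 22 patients leave after period 1, 16 from verum-first and 6 from placebo-first, so that 38 and 48 complete.
- With all observed data and no correlation between periods, the bias per point of pi is the difference in the share of period 2 data under each treatment. Verum: 48/(54 + 48) = 0.4706. Placebo: 38/(54 + 38) = 0.4130. Difference: 0.058.
- With a correlation of 0.6, generalised least squares for the random-intercept model gives 0.101.
- An analysis of completers only gives (48 − 38)/86 = 0.116, the upper limit.

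For a 12:10 split the zero-correlation value is 44/98 − 42/96 = 0.011, and 0.020 at correlation 0.6. With a period term the bias is zero in every case.

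**How likely is the imbalance?** If dropout is unrelated to sequence, the split of 22 among 54 + 54 is hypergeometric. The probability of a split at least as uneven as 14:8 is 0.23, and as uneven as 16:6 it is 0.03.

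**Cost of the period term.** With a period term and 86 completers, simulated power is about 90.5% (43:43), 90.1% (38:48) and 89.5% (35:51), whatever pi is.

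**The case against.** The strongest reply is that the text is provisional. Section 13.1 lets the SAP revise the model and promises further detail there. That is so, and this point concerns only the default. But the default lists its terms in full, so the omission is stated rather than left open.

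Second, the coding of visit is not fixed. If it had four levels (visits 3, 4, 6 and 7), period would be absorbed and the bias would be zero. The wording in section 13.1 points to two levels, yet the four-level reading is not excluded.

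Third, a reader might infer that any period effect does harm. The endpoint does not support this. A level shift already present at the period baseline is subtracted out, and steady progression adds about the same six-week change in both periods. Only a difference in the change itself matters.

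Fourth, a reader might infer that the false-positive rate is inflated. With balanced sequences it falls below 5%. In a completer analysis with pi = 1.5 it is 0.052 at 38:48 and reaches 0.075 only at 35:51, a 19:3 dropout split with a probability of about 0.0002 under equal dropout.

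Fifth, the signed-rank endpoints are outside the testing hierarchy, and their methods are left to the blinded data review. No confirmatory claim rests on them.

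These replies limit the size of the point. They do not supply a reason to leave period out.

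**Conclusion.** The point holds for the default primary model, with modest impact. Under balance the cost is precision: 0.4 points of power at pi = 0.5, 1.6 at pi = 1 and 6.6 at pi = 2, the last being a period difference larger than the 1.5-point target effect. For a 16:6 dropout split the bias per point of pi is 0.06 to 0.10 SARA points, about 4 to 7% of 1.5; for 12:10 it is 0.01 to 0.02. Its direction depends on the sign of pi and on which sequence loses more patients. Material bias therefore needs both sequence-related dropout and a sizeable period difference, and the documents establish neither.

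These figures assume the two-level reading of visit, an SD of 4.2, dropout after period 1, and cross-period correlations of 0 to 0.6. The change is still worth making because it is almost free and has to be settled before unblinding.

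**What to change.** In section 13.1 and the synopsis, or by revision in the SAP, add period (1 or 2) as a fixed effect in the primary model. State that visit means week 2 or week 6 within period. Coding visits 3, 4, 6 and 7 as four levels would also absorb period, but then the protocol must say so. The cost is a change of wording, about one degree of freedom and 0 to 1 point of power if the periods do not differ.

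Optional and of lower priority: for SCAFI, the SARA items, BDI-II and FSS, compare within-patient period differences between the two sequences by a rank-sum test, and halve the Hodges-Lehmann shift to estimate the treatment effect.

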| Trial Endpoints  | 
Primary efficacy endpoint:
 
SARA total score: absolute changes at the end of each treatment period compared to the period-level baseline defined as SARA score at visit 2 (treatment period 1) and at visit 5 (treatment period 2)
 
Key secondary endpoint(s):
 
SCAFI and subscores of SARA, QoL (EQ-5D-5L), depression (BDI-II), fatigue (FSS): absolute changes at the end of the 6-week treatment period compared to the period-level baseline defined as score at visit 2 (treatment period 1) and at visit 5 (treatment period 2).
 
Additionally, change scores at follow-up visit will be assessed.
 
Assessment of safety:
 
Documentation and reporting of side effects (AEs, SAEs, SUSARs)
 |

Confidential

|                           |                                                                                                                                                                                                                                                                                                                                                                                                                                                                                                                                                                                                                                                                                                                                                                                                                                                                                                                |

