### 6.2 Primary Efficacy Endpoint

The primary efficacy endpoint is defined as the absolute changes in SARA total score from period-level baseline to the end of the 6-weeks treatment period (verum/ placebo), i.e. the difference between post-treatment values and the corresponding period-level baseline values:

$$\text{Delta (SARA}_{\text{total}}) = \text{SARA}_{\text{total}} (\text{post-treatment}) - \text{SARA}_{\text{total}} (\text{period baseline})$$

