### 13.4 Populations included in the Analysis

The primary endpoint of the clinical subject will be analysed primarily according to the intention-to-treat (ITT) principle. Amongst others, this means that, whenever possible, the subjects will be analysed according to the treatment sequence to which they were randomised, irrespective of whether they refused or discontinued the treatment or whether other protocol violations are revealed.

An analysis per-protocol (PP) for a specific endpoint excluded or censored endpoint information considering major protocol deviations potentially effecting subjects' specific endpoint value, e.g. in the case of major violation of eligibility criteria, lack of sufficient treatment per protocol, major use of prohibited concomitant therapy, or unsatisfactory examinations or evaluations for endpoint assessment. Exclusions or censoring with respect to endpoints confirmatory analysed after unblinding of the statistician will be listed and accounted for (e.g. incidentally finding of major violation of eligibility criteria during secondary analyses). The PP analyses will be performed for the purpose of a sensitivity analysis and investigating robustness of results.

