### 13.6 Handling of Dropouts, Withdrawal, and Missing Data

Subjects dropping out of the trial prior to randomization will be listed including the reason for dropout.

Subjects dropping out totally from the study or merely from the study assigned treatments after randomization will be analysed using all available data. No multiple imputation techniques will be performed for the primary efficacy analysis which is based on an "all observed data approach".

For secondary analyses, dropouts will be included, following ITT principles, by modern imputation techniques for missing data assuming ignorable missingness (e.g. by using the multiple imputations by chained equations (MICE)-approach). For per-protocol analyses, missings will not be imputed.

Sensitivity analyses will be performed to explore several testable and untestable assumptions including various scenarios of informative missingness, in order to assess the robustness of the overall trial result. A detailed description of the applied methods to investigate assumptions concerning missingness will be provided in the *statistical analysis plan*.

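### The primary model's only baseline covariate is constant within a patient and cannot sharpen the treatment contrast; adding the period-specific baseline is a nearly free gain in precision

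*Protocol*

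**What the plan says.** Section 6.2 defines the primary endpoint as "the difference between post-treatment values and the corresponding period-level baseline values". The Synopsis sets the two period baselines as the SARA scores at visit 2 and visit 5.

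Section 13.1 writes out the default primary model, which the SAP may revise. It is a linear mixed model for this change, with treatment, visit and treatment-by-visit as factors, "mean of both period-level baseline SARA total scores as covariate" and "normally distributed patient-specific random intercepts". The Synopsis gives the same covariate. Neither place includes the baseline of the period being analysed as a term of its own.

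On dropouts, section 13.6 says that those leaving the study or its treatments after randomisation "will be analysed using all available data", and it excludes multiple imputation from the primary analysis. Section 13.4 adds, where possible, that "subjects will be analysed according to the treatment sequence to which they were randomised".

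**The concern.** A baseline covariate in a crossover model is normally there to reduce the noise in the treatment effect. This one cannot do so. The mean of visits 2 and 5 is the same number in both of a patient's periods, so it describes differences between patients only, and the treatment effect is estimated almost wholly within patients. What remains is the change score, which subtracts each period's baseline in full. If the baselines carry measurement error or short-term fluctuation, full subtraction adds that noise to the contrast, whereas an estimated slope would subtract only as much as helps.

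At stake is precision from data already collected at visits 2 and 5. A second, smaller matter is that a mean of two values is undefined for a patient with no visit 5, while section 13.6 wants all available data used.

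**Working it through.** **Inputs.** From section 13.3: difference 1.5 points, SD of individual change 3.0, SD of the within-patient difference 4.2, two-sided level 0.05, power 90%, paired t-test, 86 completers, about 20% dropout, 108 randomised. Not in the protocol: r, taken here over the range 0 to 1.

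**1. The plan's own figure.** Noncentral-t power for a paired t-test with 1.5/4.2 gives n = 85, and 90.6% power at 86. Dropout: 86/0.80 = 107.5, so 108. Both figures reproduce.

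**2. The covariate cancels.** Write m for a patient's mean baseline and b for its coefficient. The covariate adds b·m to the verum response and b·m to the placebo response, so their difference contains b·m − b·m = 0. In one simulated data set of 108 complete patients, the week-6 treatment estimate was −1.8557 with SE 0.3639, both with and without the covariate.

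**3. What a period-specific term would do.** Let X1, X2 be the period baselines and Y1, Y2 the week-6 scores. Assume Var(X1−X2) = Var(Y1−Y2) = T, with correlation r between the two differences.

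- Change-score contrast (slope fixed at 1): variance = T + T − 2rT = 2T(1−r).
- Contrast with estimated slope: variance = T(1−r²).
- Ratio = (1−r²)/[2(1−r)] = (1+r)/2.

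**4. Size.** The SD after adjustment is 4.2·√((1+r)/2):

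| r (assumed) | SD | n for 90% power | power at 86 |
|---|---|---|---|
| 0 | 2.97 | 44 | 99.6% |
| 0.4 | 3.51 | 60 | 97.5% |
| 0.6 | 3.76 | 68 | 95.6% |
| 0.9 | 4.09 | 81 | 91.9% |
| 1 (limit) | 4.20 | 85 | 90.6% |

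The degree of freedom spent on the slope is ignored.

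**5. Check by simulation at r = 0.** There were 150 trials of 86 completers, with equal correlation among all visits and within-patient variance 4.5 per measurement, so that the change SD is √(2×4.5) = 3.0. The empirical SE was 0.470 with or without the mean covariate, and 0.354 once the period baseline was added. Theory gives √(4×4.5/86) = 0.457 and √(2×4.5/86) = 0.323. An SE from 150 replicates has a relative error of about 6%, so the results agree within simulation error.

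**6. The planning figures do not fix r.** The SD of 4.2 is close to 3.0×√2 = 4.24, which means uncorrelated period changes. Suppose measurements correlate ρw within a period and ρb between periods. The covariance of the two changes is then proportional to ρb − ρb − ρb + ρb = 0, whatever ρw is, while r = (ρw − ρb)/(1 − ρb). Uncorrelated changes therefore fit any r from 0 upwards. The 0.6 in section 13.3 is called an intra-patient correlation and is not identified as r. If it were the correlation between period changes, the SD would be 3.0×√(2×0.4) = 2.68 and n would be 36. The ratio in step 3 holds either way; the n column depends on 4.2.

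**7. No visit 5.** The upper bound is 108 − 86 = 22 patients, if all assumed dropout came before visit 5. In one simulated data set with 22 such patients, deleting them left 86 patients (SE 0.410); using the available baseline kept 108 (SE 0.388). By generalised least squares with uncorrelated period changes of SD 3.0, adding 11 or 22 period-1-only patients to 86 completers moves the SE from 0.458 to 0.444 or 0.431, and power from 90.6% to 92.2% or 93.6%. At a correlation of 0.6 between changes, 22 such patients move the SE only from 0.289 to 0.282.

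**The case against.** **The plan is internally consistent.** The endpoint is a change score, and the size was computed for that change "using a paired t-test with a 0.05 two-sided significance level"; section 13.3 says the resulting number "is needed to have 90% power to detect a difference in means of 1.5". Nothing there relies on the extra term. This stands. A reader might infer that the trial is underpowered because of the covariate, and the documents do not support that. The 90% is reached with 86 completers on the unadjusted contrast.

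**The gain is unknown.** This also stands. It runs from half the variance to nothing, and the r = 0 figures are an end of the range, not a forecast.

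**The SAP may settle it.** Section 13.1 allows the SAP to revise the model. How a covariate is formed when one component is missing is ordinary SAP content and would not be a finding alone. But the list of fixed effects is written out as the default, so the choice of covariate can fairly be judged as it stands.

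**Dropouts need not be lost.** A reader might infer that everyone who stops in period 1 falls out of the intention-to-treat analysis. Sections 10.2.6 and 16.2.1 let a patient who stops treatment in period 1 go on to visit 5 and period 2, so only those who never reach visit 5 are concerned. Even for them, deletion is what software does by default with a missing covariate; the protocol does not call for it. Section 13.6 can be read as asking for whichever baseline exists.

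**Carry-over.** It is tempting to present a slope below 1 as protection against a residual period-1 effect at visit 5. That holds only if the effect has faded by the period-2 visits. If an effect c persists equally at visits 5 and 7, the change score removes it (c − c = 0), whereas a slope b below 1 leaves (1−b)c.

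**Conclusion.** The concern holds as a missed improvement in the default primary model. In patients with both periods, the only baseline covariate has no influence on the treatment contrast. Adding the period-specific baseline multiplies the contrast variance by (1+r)/2: a saving of 50% at r = 0, 20% at r = 0.6, 5% at r = 0.9 and none at r = 1. This rests on equal variances of the baseline and post-treatment differences, on an r that the protocol does not give, and on the wash-out being sufficient, because visit 5 follows randomised treatment.

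It is not a shortfall in power, not a demonstrated exclusion of randomised patients and not an answer to carry-over. The tension between a mean of two baselines and the use of all available data is real but secondary. It affects at most 22 of 108 patients, and only if all assumed dropout came before visit 5.

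**What to change.** In section 13.1 and the Synopsis, or in the SAP before unblinding:

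- Keep the mean baseline and add a second covariate, the period baseline minus the patient's mean baseline. The response stays the change score, so the endpoint in section 6.2 and the sample size in section 13.3 are untouched.
- Define the mean baseline as the mean of the available period baselines, that is, visit 2 alone where visit 5 is missing. The added covariate is then zero for that patient, and the period-1 data remain in the primary model, as section 13.6 asks.
- Report the estimate without the added term as a sensitivity analysis, since the two versions respond differently to a residual effect at visit 5.

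The cost is two sentences and one model term, with no new data or visits.
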